### 2.3. Description of the Study Intervention

The intervention is underpinned by a framework of how to create a mentally healthy workplace [69] by employing an integrated approach [82]. The development of the intervention has been informed by several systematic reviews designed to understand organisational mental health interventions in the construction, healthcare, and ICT sectors, a systematic review to identify the facilitators and barriers to the implementation of mental health promotion interventions delivered in workplace settings [83], and a consultation survey with key stakeholders in the three sectors and academia.

The study intervention is designed to improve mental health in the workplace, reduce stigma and promote mental wellbeing. The intervention is facilitated through the MENTUPP Hub, an online platform that presents interactive psychoeducational materials, toolkits, and links to additional resources in an accessible and user-friendly manner (See Figure 2).

Although the MENTUPP intervention was originally planned to be delivered in a hybrid form (i.e., online and face-to-face), all of the materials are delivered online to facilitate participation and engagement during periods of coronavirus disease (COVID-19) restrictions. The material includes online information packages, videos, pre-recorded roleplays, animated scenarios showing case studies, short quizzes, reflection exercises, breathing and mindfulness exercises, and practical stress management exercises. Research shows that having coping strategies may prevent occupational burnout [16]. The Hub is designed to give tailored content to the construction sector, the healthcare sector, and the ICT sector with examples typically experienced within the sectors and presented in videos and animated scenarios by workers from each of the sectors. Within each sector, the Hub provides general material on mental health, wellbeing, and anti-stigmatisation, as well as focused material and tools for employees and for leaders/managers. Participating workplaces are encouraged to employ the materials they engage with in the Hub in their everyday working life.

For the purpose of the pilot study, the MENTUPP Hub will be available in the following languages: Albanian, Dutch, English, German, Hungarian, and Spanish. Materials in the MENTUPP Hub will be delivered to participants via three intervention components that participants will navigate through themselves. Intervention component A focuses on promoting mental wellbeing and targeting non- and pre-clinical mental health aspects including stress, burnout, and depressive symptoms. It involves the presentation of materials that develop the participants’ general understanding and awareness of mental wellbeing, stress, and burnout, as well as a mental wellbeing and stress management toolkit. Leader-specific materials relate to organisational factors associated with wellbeing and teaches communication skills to supervisors on how to address psychosocial aspects of work with employees and develop action plans for modifying the psychosocial work environment. Employee-specific materials relate to stress management and peer support in the workplace with practical guidance on how to build peer support structures supported by video case studies of lived experiences.

Intervention component B is focused on depressive disorders and co-morbid anxiety. It is comprised of psychoeducational materials aimed at gaining a general understanding of what depression and anxiety are, as well as what factors are involved in their onset and maintenance. There are useful tips for users and advice on where to seek further help if necessary. A distinct toolkit for supervisors covers more specific topics including the business impact of these mental illnesses, information on suicide prevention, and guidelines for helping employees in different situations.

Intervention component C aims to target stigma in the workplace and is comprised of psychoeducational materials for all users including lay helpers and sufferers. An overview of the aims, content, and delivery of each component are detailed in Table 1.

### 2.4. Procedure

The research officers in each country will follow the standard operating procedure in the recruitment and implementation of the intervention. Each intervention country will have a local steering committee, comprised of key stakeholders of the sector, experts in workplace mental health promotion, and academia. Potential SMEs will be identified by local steering committees by giving feedback on recruitment (including the identification of potential SMEs) and information materials and facilitating the establishment of links between the local research officer and potential participating organisations. Standard operating procedures will be developed by the research team to guide the recruitment of the companies with specific focus on how to secure commitment from senior management to support and promote the project. The standard operating procedures will also include specifications of minimal commitment expected of companies to participate. To assess if the enterprise is suitable and able to meet the minimum requirements of commitment for participation in the MENTUPP pilot study, the local research officer and a local SME staff member will complete a pre-implementation assessment. The minimum commitments required from SMEs include:(a)the agreement to develop a project planning group, with the local research officer, local SME representatives, and a local MENTUPP ‘champion’ (a designated employee within the participating SME who will be leading on the promotion, engagement, and implementation of the project),(b)the understanding that data on individuals will be kept confidential, will not be shared with the SME, and will only be fed back in aggregated form to provide a high-level overview of how participants responded to the survey,(c)the permission from management for employees to engage with the intervention during paid work hours.

In addition, the pre-implementation assessment will capture the enterprise’s activities in relation to mental health as well as company characteristics such as the number of employees, first language spoken by employees, etc. Once an SME has been recruited, the lead investigator and local research officer will deliver a brief introductory session either face-to-face or online (depending on local COVID-19 restrictions) to employees and employers two weeks prior to intervention implementation. The local research officer will describe the purpose of the study, the scope and nature of the intervention tools, an overview of the questionnaire, and will highlight the opportunity for participants to take part in focus groups after completing the intervention. Employees will be explicitly told that their decision to participate will not impact their position within the company in any way and their details will not be shared back with management of the organisation. All potential participants within an SME will be given an information leaflet with basic information about the study and will be given the opportunity to ask any questions. The information leaflet will provide contact details for the local research officer should they have any questions. Following receipt of this information leaflet, participants will be asked to give consent for participation in the study by completing an online form.

**Table 1 ijerph-19-00947-t001:** Overview of the aims, content, and delivery of MENTUPP components.

Module	Aims/Objectives	Material Type(s)	General Material	Sector Specific Versions of the Material	For Employees	For Supervisors
Understanding Mental Wellbeing, Stress and Burnout	To better understand mental wellbeing, stress, and burnout; How to apply 3 approaches for promoting mental wellbeing and preventing mental health problems: proactive, responsive, and reactive; To identify what everyone in the organisation can do to support mental health and wellbeing.	Online written material		YES	YES	YES
Toolkit: Mental Wellbeing and Stress Management	Increase your understanding of mental wellbeing and how it can be strengthened; Increase understanding of stress, how it impacts thoughts and emotions; Introduce practical exercises for managing stress, breathing and mindfulness.	Online written material, reflective exercises, practical exercises		NO	YES	YES
Toolkit: Supervisor Training- Creating Mentally Healthy Workplaces	1. To better understand mental wellbeing, stress, and burnout in the context of the workplace;	Online written material,		YES	NO	YES
	2. To identify and screen for factors in the psychosocial work environment that may be influencing mental wellbeing, stress, and burnout at your workplace;	Reflective exercises,				
	3. To understand how to engage your staff in conversation about psychosocial work environment factors influencing their mental wellbeing, stress, and burnout;	Practical checklists				
	4. To develop action plans to address relevant psychosocial work environment factors influencing mental wellbeing, stress, and burnout in your staff.	Interactive scenarios				
Toolkit: Supporting Each Other at Work	To deepen understanding of peer support and what it entails; Broaden your ability to develop and strengthen it within your workplace.	Online written material, Videos, Practical Exercises Resources		YES	YES	NO
Understanding Depression and anxiety	To better understand depression and anxiety;	Online written material	YES	NO	YES	YES
	2. To learn about the impact of depression and anxiety on work	Videos				
	3. To get to know the different treatment options.	Interactive learning activities				
Toolkit—Supervisor Training—how to address mental illness in the workplace	Understand the business impact of depression and anxiety. Have a conversation with an employee who you think might be depressed or anxious. Support someone who has suicidal thoughts in getting help. Support an employee who has had mental health-related sick leave to successfully return to the workplace.	Online written material, Videos, Practical Exercises	YES	NO	NO	YES
Challenging stigma—a guide for employees and leaders	To better understand stigmatization on the workplace, and how to cope with it.	Online written material	YES	NO	YES	YES
Challenging stigma—a guide for people with mental health issues	To better understand stigmatization, and how to react when being stigmatized. To learn communicational skills to talk about mental health problems.	Online written material	YES	NO	YES	YES
Understanding stigma and discrimination—for all	To better understand stigmatization and possible coping strategies.	Online written material	YES	NO	YES	YES
Test your stigma!	To test the level of stigma.	Online written material	YES	NO	YES	YES

SMEs will meet with the local research officer in their country either face-to-face or online (depending on local COVID-19 restrictions) to discuss what participation entails for the organisation. When an SME agrees to participate in the study, participants from the SME who fulfil the inclusion criteria will be invited to participate in the intervention delivered via the MENTUPP Hub. Participants will be given the opportunity to engage with the materials in the MENTUPP Hub preferably during work hours over a six-month period (in order to view all the content of the Hub, it has been estimated that each user should spend an average of 18–20 min per week). Workplace management will play a role in encouraging engagement with and ‘championing’ the MENTUPP intervention. A pilot planning group will be established within each SME to facilitate the SME in fulfilling their duties in relation to the promotion and engagement of the intervention within the SME. Participants will also have the option of engaging with the intervention in their own free time.

Participants will access the intervention through their personal or work electronic devices (e.g., laptop, computer, smartphone, tablet) at a time of their workday that is allowed by the SME. Participants can also access the intervention from their personal devices at any time of their preference outside of work. Participants will be encouraged to use the skills and knowledge they learn in their working life, in minding their own mental health and in their interactions with their colleagues. Leaders will be encouraged to use the MENTUPP materials in their day-to-day management of the workplace. The pilot planning group within each SME will meet regularly with the research officers to discuss progress in promoting engagement within the SME and to address any issues or barriers that may appear in the process of implementation. The research officers will guide these sessions based on the steps outline in the standard operating procedure. The research officers will feed back to the larger consortium on a weekly basis to present updates and to discuss any issues that arise. Weekly meetings will ensure standardization in addressing any unanticipated issues that may arise during the pilot implementation process. Implementation of the intervention involves flexibility in terms of how the workplace promotes and engages with the MENTUPP Hub. Flexibility is required at this point of the research process given that little is known about what influences managers and what is required for successful implementation of such an intervention [84]. All actions taken as part of the implementation process will be recorded and will contribute to the standard operating procedure of the cRCT at a later point.

### 2.5. Data Collection

Both quantitative and qualitative data will be gathered as part of this pilot study, supporting both pre-post outcome and process evaluations. The data collection and analysis of the pilot study is guided by the RE-AIM framework [29] and will map across the five dimensions of the framework—reach, effectiveness, adoption, implementation, and maintenance. Furthermore, this study will consider the acceptability, appropriateness, and feasibility of the intervention [30].

The process evaluation will examine the process of implementation (whether and how planned activities took place) and the preliminary outcome evaluation will examine whether the expected results and effects of the intervention can be achieved.

#### Process Evaluation

The process evaluation will adopt a combination of the RE-AIM framework [30] and the evaluation framework outlined by Proctor and colleagues [31]. Data will be gathered from multiple sources: self-developed surveys, validated scales, a monitoring instrument, online log data of users, and focus groups with leaders, employees, and local research officers responsible for implementing the MENTUPP intervention in the intervention countries. The Organizational Culture Assessment Instrument (OCAI) [32] will be administered at baseline only from a selection of managers and will be used to understand the culture of, and the presence of psychosocial risk factors and stressors in the SMEs. Information at organisational level will be collected from a designated employee in a supervisory or management position from each SME using a monitoring instrument developed by the MENTUPP consortium. The instrument collects quantitative and qualitative information of the SME at the time of recruitment (general information on the SME and staff, experience with mental health problems in the SME, how the SME deals with employee mental health issues, the impact of COVID-19 on the SME) and information on the adoption and implementation of the MENTUPP intervention throughout the pilot study (relevant events or changes in the SME and the country, relevant information with respect to the planned activities, etc.).

Three surveys including internationally validated measures tailored to the specific evaluation needs of the MENTUPP pilot study will be used to collect information at the individual level at baseline and follow-up. The pre-intervention survey will be administered to all employees and gather information relating to the following themes: sociodemographic and work-related information; ways of approaching mental health difficulties in the organisation; experience with mental health difficulties; expectations of the MENTUPP intervention; acceptability, appropriateness, and feasibility of MENTUPP at baseline and follow-up; and the impact of COVID-19 on mental health and the workplace. A post-intervention survey for employees will ask participants for specific feedback on their views and experiences of participating in MENTUPP and on their views of the MENTUPP Hub on completion of the intervention period. A post-intervention survey for leaders will assess the extent to which activities recommended by MENTUPP are initiated in the SME (e.g., better work planning, more peer support, regular meetings, etc.).

Log data on user activity tracked via the MENTUPP Hub will be collected to compile information on how frequently the MENTUPP Hub was used and which parts of the platform were most frequently accessed.

Internationally validated questionnaires (listed below) will be administered during facilitated sessions at baseline before access to the MENTUPP Hub is given, and again at the end of the 6-month pilot intervention period. The following self-report, standardised measures of wellbeing and mental health will be included:○Mental wellbeing and quality of life: The World Health Organisation—Five Wellbeing Index (WHO-5) [85]○Depression and anxiety: Patient Health Questionnaire Anxiety and Depression Scale (PHQ-ADS) [86]○Depression stigma: Depression Stigma Scale (DSS) [87]○Presenteeism in the workplace: Stanford Presenteeism Scale (SPS-6) [88]○Productivity: Work Productivity and Activity Impairment—General Health V2.0 (WPAI-GH 2.0) [89]○Burnout: Oldenburg Burnout Inventory (OLBI) [38,90] ○Help-seeking behaviour: Attitudes Towards Seeking Professional Psychological Help-Short Form (ATSPPH) [91]○Presence (level) of psychosocial risk factors and stressors: Selected items and scales from the Copenhagen Psychosocial Questionnaire (COPSOQ) [92]

Following the intervention period, focus groups will be conducted to gain more in-depth qualitative information on the quality and intensity of the pilot implementation of the intervention in each of the intervention countries. Information on the perspectives and experiences of employees and employers who engaged with the intervention, as well as the barriers and facilitators to implementation of the intervention will be obtained. Separate focus groups will be conducted with employees and with supervisors/managers in the participating SMEs. These focus groups will provide in-depth information with respect to the strengths and the weaknesses of the content of the MENTUPP Hub including the acceptability, comprehensibility, feasibility, appropriateness, relatability and uptake of the content, and barriers and facilitators of the implementation of the MENTUPP intervention tools. There will be also a focus group with the local research officers of each country, to discuss the experiences with the recruitment of SMEs, barriers, facilitators, and experiences of, implementation, and areas of improvement for the implementation and evaluation of the MENTUPP intervention. In every country, at least one focus group with 3–5 leaders across organisations (i.e., managers, supervisors, health and safety professionals) and one focus group with 8–10 employees will be organised based on previous research with focus groups [93]. These focus groups will discuss communication of the MENTUPP intervention within the SME, experiences of using the MENTUPP Hub, areas for improvement to either the intervention, evaluation, or both, and the extent to which activities recommended were initiated in the workplace.

### 2.6. Data Management

The survey data will be collected via Qualtrics (Provo, UT), which is a General Data Protection Regulation (GDPR) compliant online platform. Participants will create their own unique identifier that will allow researchers to link their evaluation data to their activity on the MENTUPP Hub. Any personal information collected (e.g., email address/phone number) required in accessing the Hub will be stored separately from evaluation data. The information that participants provide will be aggregated for analysis by SME/sector depending on the number of cases and an individual’s data will not be fed back to SME management. Qualitative data will be collected by local research officers.

### 2.7. Data Analysis

#### Process and Preliminary Outcome Evaluation

The self-reported surveys (including validated questionnaires) and monitoring instruments collected pre- and post-intervention will be analysed using descriptive statistics and non-parametric and parametric tests. Patterns of completeness in the survey will inform the development of the self-reported surveys (including validated questionnaires) to be used in the cRCT. The log data from the MENTUPP Hub will also be analysed to establish patterns of engagement by calculating the number of participants visiting the Hub more than once, the total number of visits to the Hub overall and on an individual level, and the total time spent accessing and engaging with the content.

Qualitative data of the focus groups will be audio recorded, transcribed, and analysed using thematic analysis [94] to explore patterns in qualitative data across participants and across sectors. Themes and subthemes will be determined as the overarching categories of common data across multiple participants.

Quantitative and qualitative data will be interpreted in relation to each sector as well as each intervention country to understand the implementation of the intervention within each context. This information will be used to optimise the intervention for the cRCT.

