## 2. Materials and Methods

### 2.1. Study Design

This pilot study will involve both quantitative and qualitative measures to evaluate the delivery of the MENTUPP intervention and relevant tailored materials in the construction, healthcare, and ICT sectors, and within each country using colloquial and everyday language of the intervention country. The study design will be a non-randomised, uncontrolled pre- and post-intervention process evaluation (and preliminary outcome evaluation). MENTUPP is a complex, multilevel intervention [77,78,79] which entails multiple sources of data collection (surveys, a monitoring instrument, log data of users, and focus groups with leaders, employees, and local research officers responsible for implementing the MENTUPP intervention in the intervention countries) to examine the delivery and implementation of the intervention in different organisational and cultural settings. This study represents one aspect (feasibility and piloting) of the broader MENTUPP project which aims to develop, implement, and evaluate a workplace-based, mental health promotion intervention (see Figure 1).

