#### 2.2.3. Sample Size

One of the aims of this pilot study is to estimate the level of attrition expected in the cRCT [79]. Each of the nine intervention countries will recruit 1–3 SMEs in one of the three sectors (construction/healthcare/ICT) aiming to recruit approximately 60–70 participants (employees and managers) in each intervention country. This sample size allows for an attrition rate of 62–67%, ensuring at least 23 complete sets of data across the intervention (pre- and post-intervention) within each country. With a sample of approximately 600 participants and accounting for 60% attrition, the 95% confidence interval for those lost to post-intervention would be 56–64%, i.e., a margin of error of 4%.

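### Pre/post tests in an uncontrolled pilot expecting about 60% loss cannot show whether the intervention's effects can be achieved, and the limitations do not say so

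*Protocol article*

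**What the plan says.** - Section 2.1 calls the design a "non-randomised, uncontrolled pre- and post-intervention process evaluation", with a preliminary outcome evaluation alongside.
- Section 2.5 sets the aim of that second part: "the preliminary outcome evaluation will examine whether the expected results and effects of the intervention can be achieved".
- Section 2.7, whose subheading covers both the process and the preliminary outcome evaluation, says that the surveys (validated questionnaires included) and the monitoring instruments "will be analysed using descriptive statistics and non-parametric and parametric tests".
- Section 2.2.3 plans 1 to 3 SMEs in each of nine countries. Its precision statement begins "With a sample of approximately 600 participants and accounting for 60% attrition". Its per-country allowance reads "This sample size allows for an attrition rate of 62–67%, ensuring at least 23 complete sets of data".
- The end of the Introduction makes feasibility, acceptability and uptake the central aim. None of the four specific objectives is a test of effectiveness, but one is to estimate parameters for the power calculation of the later cluster randomised trial (cRCT).
- Strengths and Limitations discusses COVID-19 as an obstacle to participation, recruitment and implementation, self-selection that may understate effectiveness, and the weaknesses of self-report. It does not mention the missing control group, time trend, regression to the mean or selective loss as limits on reading the pre/post change.

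**The concern.** A question about intervention effects is put to data that have no comparator. Over six months the scores may move for several other reasons:

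- **Time trend.** The article's own Introduction and Conclusions say that COVID-19 affects mental health, which is what the questionnaires measure.
- **Regression to the mean.** This arises if people join when they feel worse than usual.
- **Selective retention.** This arises if the minority who complete the second survey differ from those who do not.

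A paired test reports only that the completers changed. Section 2.7 also says that the quantitative and qualitative findings will be used to optimise the intervention for the cRCT. A significant change could therefore be carried forward as evidence of effect or as a planning effect size. A null result, particularly at about 23 pairs in a country, could count against useful content.

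**Working it through.** **The plan's own figures.** Both reproduce.

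- Precision of attrition: 0.60 ± 1.96 × √(0.6 × 0.4 / 600) = 0.60 ± 0.039, or 56.1% to 63.9%. The article gives 56–64% and a margin of 4%.
- Per-country allowance: 1 − 23/60 = 61.7% and 1 − 23/70 = 67.1%. The article gives 62–67%.

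The section gives no comparable figure for any outcome measure.

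**Pairs available.** 600 × 0.4 = 240. At the per-country minimum, 9 × 23 = 207. The number of SMEs is 9 × 1 = 9 to 9 × 3 = 27.

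**No control group.** Suppose the true intervention effect is zero and scores drift by d SDs of change for other reasons (d is assumed; the article gives none). The probability that a two-sided 5% paired test is significant is Φ(d√n − 1.96) + Φ(−d√n − 1.96).

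| Drift d | n = 207 | n = 240 |
|---|---|---|
| 0.1 | 0.30 | 0.34 |
| 0.2 | 0.82 | 0.87 |
| 0.3 | 0.99 | 0.996 |

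For d = 0.2: 0.2 × √207 = 2.88 and 0.2 × √240 = 3.10. Subtracting 1.96 leaves 0.92 and 1.14.

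**Selective loss.** Mean change over all participants = 0.4 × (change in completers) + 0.6 × (change in those lost). If completers improve by 0.2 SD and those lost do not change (assumed), it is 0.4 × 0.2 = 0.08 SD. It is zero if those lost worsen by 0.2 × 0.4/0.6 = 0.13 SD. The completers' data cannot distinguish these cases.

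**Clustering, if the tests ignore SME.** The article does not say whether they do. With m = 240 / (number of SMEs), the design effect is DE = 1 + (m − 1) × ICC, and the true error of a nominal 5% test is 2 × [1 − Φ(1.96/√DE)]. The ICC of change is assumed.

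| SMEs | m | DE, ICC 0.02 | Error | DE, ICC 0.05 | Error |
|---|---|---|---|---|---|
| 9 | 26.7 | 1.51 | 11.1% | 2.28 | 19.5% |
| 18 | 13.3 | 1.25 | 7.9% | 1.62 | 12.3% |
| 27 | 8.9 | 1.16 | 6.9% | 1.39 | 9.7% |

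The range is about 7% to 20%.

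**The case against.** The strongest reply is that this is a feasibility pilot. The evaluation is labelled preliminary, the text asks whether effects can be achieved rather than whether they were, descriptive statistics come before tests, and sizing the study on attrition suits its aims. An article may also leave the choice of test and any adjustment for SME to a fuller document. Much of this stands. It confines the point to a secondary evaluation and makes the clustering figures conditional. It does not remove the mismatch between purpose and design, because no later choice of test supplies a comparator.

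A reader might infer more than the article supports:

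- *That COVID-19 is ignored except as a barrier to engagement.* Section 2.5 has the pre-intervention survey ask about its impact on mental health and the workplace. The monitoring instrument records its impact on the SME at recruitment, and relevant events in the SME and country during the pilot. Such data describe the context but do not replace a control group.
- *That all baseline responses will be compared, unpaired, with all follow-up responses, so that a baseline difference between retained and lost participants appears as change.* Section 2.2.3 counts complete pre/post sets and section 2.8.2 provides a code linking time points, so a paired analysis is possible and looks intended.
- *That every instrument will be tested in every sector and country.* Section 2.7 says that data will be interpreted by sector and country, not tested in each.
- *That the pre/post change is already fixed as the cRCT effect size, or that content will be dropped on a null test.* The article states neither. The power parameters are not named, and optimisation also draws on the qualitative data.

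**Conclusion.** The concern holds for the preliminary outcome evaluation. The article fixes an uncontrolled pre/post design, gives that evaluation a question about intervention effects, assigns significance tests to the questionnaires, and omits the decisive limits from its limitations section.

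The 0.82 to 0.87 chance of a significant result at zero effect rests on an assumed drift of 0.2 SD of change and on treating pairs as independent. The fall from 0.2 to 0.08 SD rests on assuming no change in those lost. The 7% to 20% error rate rests on an assumed ICC of change of 0.02 to 0.05 and on tests that ignore SME. The 60% loss is itself a planning allowance. The conclusion that the tests cannot identify an effect needs none of these values. The aims on feasibility, acceptability, uptake and attrition do not depend on these tests.

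**What to change.** 1. In section 2.5, restate the purpose: the preliminary outcome evaluation will describe change in the outcome measures and estimate their variability; change will not be attributed to the intervention or used as the cRCT effect size.
2. In section 2.7, replace significance tests of effect with mean paired change and 95% confidence intervals that allow for clustering of change by SME. Use an SME-level random time effect, or cluster-robust errors with a small-sample correction, since there may be as few as 9 SMEs. Random intercepts for SME alone would not do this, because they cancel from within-person change.
3. Tabulate baseline scores of retained and lost participants.
4. Add the missing control group, time trend and selective attrition to the limitations.

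The cost is wording and analysis on data already planned. The study gives up p-values that could not be read as effects, and its intervals widen. With 240 pairs, the half-width ignoring SME is 1.96/√240 = 0.127 SD of change. Multiplying by √1.16 to √2.28 gives about 0.136 to 0.191 SD under the assumed ICCs, before any small-sample correction.
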